#### 3-month and 6-month data

We will collect primary and secondary outcome data at both the 3- and 6-month time points post the time of baseline data collection.

In addition, we will collect information on the number and type of education support activities (as described in the program logic model; see Figure 2) that were received by the young person, his or her parent/s, and the school for both the intervention and control groups.

#### Stakeholder interviews

Aim 4 of the study is to obtain feedback from stakeholders about the feasibility of conducting a larger-scale trial based on the experience and learnings of the feasibility study. The lead researcher will conduct semi-structured interviews with two key stakeholders who have been involved in the study at each of the five sites in order to obtain information about their experience of the implementation of the feasibility study and learnings.

### Data Analysis

The primary and secondary outcomes form the dependent variables in this research. The independent variables include being in receipt of the intervention or not being in receipt of the intervention (i.e., membership of either the intervention or the control group).

Quantitative data will be analyzed descriptively. Continuous or scale data will be analyzed using analysis of variance (ANOVA), and we will report group means and standard deviations. We will control for confounders as previously described. We will use the data and variables of the number and type of education support activities as a measure of dose and perform sensitivity analysis. Qualitative data obtained from stakeholder interviews will be analyzed thematically.

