## Method

### Study Design and Setting

Many researchers (e.g., Chalmers, 2005; Gray, 2001; Littell & Shlonsky, 2010; Shlonsky & Gibbs, 2004) consider the randomized controlled trial (RCT) the “gold standard” in effectiveness evaluations as it is viewed to be the best design for minimizing the influence of bias. But for many others in the pedagogical community, the debate on this point is still open (Biesta, 2007). In our circumstance, given that access to a quality education is a right of the child along with the potential public sensitivity of randomly allocating hospitalized children and young people to either receive education support or not while in hospital, an RCT may not be considered either appropriate or ethical.

Fortunately, other controlled study designs are available for consideration. Controlled studies (i.e., studies with both an intervention group and a well-matched non-intervention or control group) are considered best for evaluating the effectiveness of an intervention because they state the counterfactual. That is, they investigate and compare both what happens if a group of people receive the intervention and what happens if a group of people don’t receive the intervention. This, in turn, allows stronger and more robust claims of causality and effectiveness of a given intervention; that is, that any differences in results between the two groups were due and can be attributed to the intervention (Chalmers, 2005; Shlonsky & Gibbs, 2004).

One such design is that of a controlled cohort study, where both the intervention group and the control group exist “naturally” in the community. Such is the case in Victoria, Australia, where the Department of Education and Training (DET) funds education support programs at some, but not all, pediatric hospitals and departments. The DET funds education programs at two pediatric hospitals (Royal Children’s Hospital and Monash Children’s Hospital), but not four regional pediatric departments in hospitals in Warrnambool, Ballarat, Gippsland, and La Trobe. Children and young people with chronic illnesses admitted to the latter hospitals where there is no funded education support program, therefore, naturally form the control or comparison group.

The subjects for the current study consisted of the children and young people under treatment for a chronic health condition at the Royal Children’s Hospital (the intervention group) and the four regional hospitals.

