### Intervention to Be Tested

The education support program at the Royal Children’s Hospital (RCH) in Australia is funded by the Victorian DET and employ qualified teachers to work with hospitalized young people/students to help maintain engagement with the students’ regular schools and peers, and engagement in education and learning. The Education Institute teachers evaluate new patients to determine the appropriate level of educational support. Evaluations are based on need or educational risk, with eligible students being offered individual or group learning sessions, or a combination of both. Each student receives an Individual Learning Plan (ILP) prepared in collaboration with the student, families/carers, and the enrolled educational setting. The ILP is reviewed regularly and updated in line with the student’s educational progress. The hospital kindergarten program is led by qualified early childhood educators who, through engaging play-based learning, help prepare children for school. To be eligible for the program, children must be at least 4 years old before April 30 in the year of enrolment. The Education Institute offers an evidence-based program built on high-impact teaching strategies, with a focus on literacy and numeracy underpinned by the Victorian Curriculum.

Elements of the education support program are described in a program logic model developed in consultation with staff from the Centre for Program Evaluation at the University of Melbourne. It depicts a socio-ecological approach that recognizes the influence of a number of spheres within which the child functions on a daily basis (Bronfenbrenner, 1995). These include the spheres or levels of the individual, family, schools, community and service systems. (For more detail, see Figure 2: Logic Model of an Education Support Program for Children and Young People with a Chronic Health Condition; Barnett, 2018.) The key activities and variables of the intervention across the first three spheres are listed in Table 1. Finally, the education support model at the RCH also reflects the five common themes of pediatric hospital-based education support programs as described in the introduction.

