### Recruitment and Consent

Approval to undertake the feasibility study will be sought from the Victorian DET. Once such approval has been obtained, all five pediatric sites (one pediatric hospital as the intervention site and four regional hospitals with pediatric wards as the control sites) will be approached by the lead researcher and invited to participate in the feasibility study. Once consent has been obtained from these two levels, we will proceed with the rolling recruitment of individual young people. Specifically, all new inpatients as they present to hospital and who meet the eligibility criteria will be approached by the lead researcher and asked if they would participate in the trial. Both the young person and his or her parent/s or caregiver/s will receive a Plain Language Statement about the study and asked to provide written consent.

For aim number 4 (Obtain feedback from stakeholders about the feasibility of the above with the view of conducting a larger scale trial), we will identify two key stakeholders at each of the five locations and ask them to participate in semi-structured interviews with the lead researcher. The purpose of the interviews will be explained, and verbal consent will be obtained and recorded by the lead researcher.

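### The planned dose analysis is confounded by indication: support is offered by educational need, no listed confounder measures need, and the analysis does not test the robustness of the group comparison

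*Protocol article*

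**What the plan says.** Four parts of the protocol article bear on this point.

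- **Exposure.** Data Analysis says "The independent variables include being in receipt of the intervention or not being in receipt of the intervention" and explains this in parentheses as "membership of either the intervention or the control group". Study Design and Setting fixes the groups by place of treatment: "the children and young people under treatment for a chronic health condition at the Royal Children’s Hospital (the intervention group) and the four regional hospitals". Under Recruitment and Consent, "all new inpatients as they present to hospital and who meet the eligibility criteria will be approached by the lead researcher", so having had sessions is not a condition of entry.
- **How support is allocated.** Intervention to Be Tested says of the intervention hospital: "Evaluations are based on need or educational risk, with eligible students being offered individual or group learning sessions, or a combination of both". The same section gives every student an individual learning plan, and Table 1 also counts work with families and schools as key activities.
- **Dose.** The 3-month and 6-month data section records the support activities "for both the intervention and control groups". Data Analysis uses the "number and type of education support activities as a measure of dose and perform sensitivity analysis".
- **Adjustment.** Data Analysis controls for the confounders described earlier. The Confounders section lists family socio-economic position, parental involvement in education and parental mental health (DASS-21). Baseline values of both outcomes and the type of illness are collected, but they are not named there as adjustment variables. Inpatient days are not among the data items listed.

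**The concern.** If teachers offer more to children at greater educational risk, the amount of support is partly a marker of prognosis. A child who stays longer also has more opportunity to receive activities. If need or a long stay goes with poorer engagement or quality of life, a regression of outcome on number of activities mixes the effect of support with the reason it was given. None of the three named confounders, all of which describe the family or parents, measures that reason.

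The label adds to the problem. A sensitivity analysis asks whether the main result survives a change of assumption. A dose analysis asks a different question, whether children who received more did better, and its bias is not shared with the group comparison. A flat or negative slope could be read as undermining a favourable group difference when it only reflects who was offered support. Effectiveness is the first stated aim, and the study is meant to inform a larger one, so the misreading could carry forward.

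**Working it through.** **Plan's own figures.** The article gives no figure for the dose analysis. The one related figure is the planning effect of 0.3 SD, used below as the true effect. Its sample size reproduces. Assuming two-sided alpha 0.05, which is not stated, n = 2 × (1.96 + 0.84)² / 0.3² gives 175 per arm (176 by t-test) against the stated 180. Then 180 / 0.75 = 240, as stated.

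**Illustration 1: dose within the intervention hospital.** Assumptions, none from the document:
- need is standardised, and one SD of need lowers the outcome by b SD;
- dose follows an offer index that correlates 0.7 with need;
- dose = 1 + 0.5 × index, floored at zero and scaled to mean 1;
- the true slope is +0.30.

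Unadjusted slope = true slope − b × Cov(need, dose) / Var(dose). Ignoring the floor, Cov = 0.5 × 0.7 = 0.35 and Var = 0.5² = 0.25, so the ratio is 1.4.

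| b | 0.30 − 1.4b | Simulated, with floor |
|---|---|---|
| 0.1 | +0.16 | +0.16 |
| 0.3 | −0.12 | −0.13 |
| 0.5 | −0.40 | −0.42 |

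The sign changes at about b = 0.30 / 1.4 = 0.21.

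**Illustration 2: counts driven by need and stay.** Count = 6 + 2 × need + 1.5 × stay + noise. Outcome = 0.05 × count − 0.3 × need − 0.2 × stay + noise. Need and stay are taken as independent with SD 1.
- The covariance of count with the confounding part is −(2 × 0.3 + 1.5 × 0.2) = −0.9.
- With count-noise SD 2, Var(count) = 4 + 2.25 + 4 = 10.25, so the slope is 0.05 − 0.9/10.25 = −0.04.
- With noise SD 1 the variance is 7.25 and the slope −0.07. With SD 3 it is 15.25 and −0.01.
- Adjusted for need and stay, the simulated slope returns to about +0.05.
- With zero-dose controls pooled in and no group term, it is +0.02: attenuated, not reversed.

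**Main comparison by hospital.** With a true effect of 0.30 SD in children who receive sessions and the same need distribution in both groups, the expected difference is the share receiving × 0.30. That gives 0.30 at 100%, 0.24 at 80%, 0.18 at 60% and 0.15 at 50%. In simulation it was the same, within simulation error, for b = 0.1, 0.3 and 0.5. Need-based offers dilute this contrast; they do not confound it.

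**Precision.** With 40 children, less the plan's 25% attrition, 40 × 0.75 = 30 remain. The 95% interval for a dose-outcome correlation near zero is about ± tanh(1.96/√27) = ±0.36.

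**The case against.** A reader might infer that the main comparison is confounded by indication as well, because the exposure is worded as receipt, the research question also speaks of children who receive support, and activities are recorded in controls. If children were regrouped by actual sessions, the bias would be real: with 80% receiving and b = 0.3, in the setting of Illustration 1, the 0.24 SD difference would fall to 0.18. The document does not support that reading. The parenthesis in Data Analysis defines receipt as group membership, membership is set by hospital, all eligible new inpatients are approached, and nothing moves a child between groups. The activity data are assigned to the dose analysis. The assumed shares receiving sessions are not in the document either, and with a learning plan for each student plus family and school work, a child without sessions is not shown to be a non-recipient.

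On the dose analysis, the strongest defence has four parts.
- An article may leave covariates and scaling to a fuller plan. This is fair for model details. But the article itself states the dose variable, the sensitivity label and the confounder list, and these do not fit need-based allocation.
- The analysis is not said to be unadjusted. That is true, and the family variables may capture some of the need, but none measures it directly.
- No causal dose-response claim is made. That is also true, so the point concerns interpretation and labelling as well as bias.
- Reversal depends on chosen coefficients. This stands: at b = 0.1 the slope stays positive.

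**Conclusion.** The point holds for the dose analysis. As described, the association between amount of support and outcome is confounded by indication, and it is not a check on the group comparison. If need lowers outcome and raises dose, the slope is attenuated; if need predicts outcome strongly enough (beyond about b = 0.21 in Illustration 1), it is reversed. The document supports the mechanism, through need-based offers and a confounder list without need or inpatient time. The strength of the need-outcome and need-dose relations, and so the size of the bias, is assumed.

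The point does not extend to the main contrast, which is by hospital group and is only diluted by children who receive little support. Whether case mix differs between the hospitals is a separate question, not settled here.

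**What to change.** 1. Run the dose analysis within the intervention hospital only. Adjust it for the baseline value of the outcome (already collected), inpatient days and, if it is recorded, the teachers' initial evaluation of need, in addition to the listed confounders.
2. Report it as exploratory and separate from the group comparison, not as a sensitivity analysis of it.
3. As a clarification only, state that the main contrast is by hospital of recruitment regardless of sessions received.

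The cost is a change of wording and the extraction of inpatient days and any need rating. The article says teachers evaluate new patients but not that a usable rating is kept; without one, baseline outcome and inpatient days may remove only part of the confounding. The estimate will rest on about 40 children, or about 30 after the expected attrition, and will be imprecise.

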### Sample Size and Power Analysis

Sample size calculations were run to determine the number of participants required in the study to have an 80% chance of detecting a 0.3 standard deviation effect of the intervention based on the results of the outcome measures. Based on these criteria, we would need complete data from 180 participants in each arm of the study. Attrition and loss to follow-up is considered to be low, in the order of 25%.

As such, we would need to recruit 240 participants to each arm of the study. However, as this is a feasibility study, we will recruit 40 participants to each arm of the trial and evaluate the procedure used, time, and feasibility of achieving a larger sample for any future larger-scale study.

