There are two ways to score the items: (a) calculate the total level of agreement and (b) calculate a scale score for the domains and survey as a whole. We will use the latter method as we are interested in the overall mean values of both the intervention and the control groups and related standard deviations.

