### Data Collection

#### Baseline data

Baseline data will be collected by the lead researcher or hospital-based educator at the time of student recruitment to the study or within one week of recruitment. It will consist of basic demographic data of the young person (age, gender, school grade/level, type of chronic illness, cultural identity, main language spoken at home) and of the parent (socio-economic position, involvement in child’s education, and psychological stress). We will also collect baseline data on the primary and secondary outcomes using the measures described above.

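### The stated ANOVA and its adjustment set give no place to the baseline outcome scores that this non-randomised study already collects

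*Protocol article*

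**What the plan says.** The Data Analysis section takes the primary outcome (engagement) and the secondary outcome (quality of life) as dependent variables and group membership as an independent variable. It names the method: "Continuous or scale data will be analyzed using analysis of variance (ANOVA), and we will report group means and standard deviations". It then names the adjustment set by reference: "We will control for confounders as previously described".

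The Confounders section supplies that set: a composite of family socio-economic position, three items on parental involvement in schooling, and the DASS-21 for parental distress. All describe the family or parent. None is the child's own starting score.

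That score is available. The Baseline data section says "We will also collect baseline data on the primary and secondary outcomes using the measures described above", and the same outcomes are measured again at 3 and 6 months. Nowhere does the article use the baseline score as a covariate, in a change score or as a repeated measure.

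Study Design and Setting describes a cohort with naturally occurring groups: one metropolitan children's hospital that has the programme and four regional hospitals that do not.

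**The concern.** Without randomisation, nothing makes the two groups start at the same level of engagement or quality of life. Children at a metropolitan children's hospital may differ from those on regional wards in ways that family and parent variables do not capture. If follow-up scores are compared without the starting score, part of that difference appears as a programme effect, in either direction.

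Precision is also at stake. The baseline score is usually a strong predictor of the same score later, and leaving it out keeps variance that could be removed without collecting anything new. This matters with 40 children recruited per arm, because the feasibility study is meant to inform the size and analysis of a larger one.

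The point is more than detail deferred to an analysis plan. The abstract and the discussion present the statistical analysis as one of the features settled in advance, and the article names both the method and the adjustment set.

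**Working it through.** **The plan's own figure.** Sample Size and Power Analysis asks for an "80% chance of detecting a 0.3 standard deviation effect of the intervention" and concludes that "we would need complete data from 180 participants in each arm of the study". Alpha is not stated; I assume 0.05 two-sided.

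- n per arm = 2 × (1.960 + 0.842)² / 0.3² = 174.4, so 175 (about 176 with the t distribution). This is within 3% of 180.
- A one-sided 0.05 test gives 138, which does not fit.
- 180 / (1 − 0.25) = 240, the stated recruitment target.

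The stated size therefore matches a two-group comparison of means with no allowance for a baseline covariate.

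**Inputs for the check.**

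- From the article: 40 recruited per arm, 25% attrition (40 × 0.75 = 30 completers per arm) and a target of 0.3 SD.
- Assumed, because the article gives neither: r from 0.4 to 0.7, and a baseline gap of 0.3 SD (range 0.2 to 0.5).
- For scale, chance alone gives a baseline gap a standard error of √(2/40) = 0.22 SD, so 0.3 SD is about 1.3 standard errors even if the hospitals' populations were identical.

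**Bias.** If there is no true effect and follow-up depends on baseline with slope r, a comparison that ignores baseline is off by r × gap:

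| Gap | r = 0.4 | r = 0.6 | r = 0.7 |
|---|---|---|---|
| 0.2 SD | 0.08 | 0.12 | 0.14 |
| 0.3 SD | 0.12 | 0.18 | 0.21 |
| 0.5 SD | 0.20 | 0.30 | 0.35 |

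For the 0.3 SD gap this is 40% to 70% of the target (0.12/0.3 and 0.21/0.3).

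A simulation (4,000 runs per scenario, 30 per arm, gap 0.3 SD, no true effect) agrees:

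- Without baseline, the mean estimate was 0.148 SD at r = 0.5 and 0.210 SD at r = 0.7, with rejection rates of 9.1% and 12.7%.
- With baseline as a covariate, the mean estimates were −0.002 and −0.001 SD, with rejection rates of 5.6% and 4.9%.
- The adjusted estimate is unbiased here because the simulated groups differ only through the measured baseline. Real hospitals may differ in other ways.

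**Precision.** Baseline adjustment multiplies the residual variance by 1 − r².

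- Without baseline, 30 per arm: half-width = 2.00 × √(2/30) = 0.52 SD.
- With baseline, r = 0.6: 0.52 × √0.64 = 0.41 SD.
- Over the range: about 0.47 SD at r = 0.4 (√0.84 = 0.92) and 0.37 SD at r = 0.7 (√0.51 = 0.71).

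**Larger study.** The same factor applied to the article's 180 gives 152 (r = 0.4), 116 (r = 0.6) or 92 (r = 0.7) completers per arm.

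**What these figures compare.** The reference is an analysis with no covariates at all. The plan does adjust for family and parent variables, so all the figures are ceilings, provided that those variables shrink the gap rather than widen it.

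**The case against.** The strongest reply is that the article does not commit to a comparison of follow-up scores alone. It says only ANOVA, and its list of independent variables is not exhaustive. With outcomes measured at three times, a group-by-time ANOVA that includes baseline would fit the words. A journal article also leaves much of the model form to a fuller document. This stands in part: a reader might infer that the plan excludes baseline and will read pre-existing gaps as programme effect, and the text does not go that far. What remains is that the adjustment set is fixed by reference to a list without the baseline score, and nothing states the repeated-measures reading. In its usual form that reading would also drop children with a missed visit, with 25% attrition expected.

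The remedy has limits too, and these stand. Baseline may be taken up to one week after recruitment, while eligibility rests on an expected stay of five or more days. Some baseline scores may therefore follow the start of support, and conditioning on them could remove part of the effect. The engagement form was shortened on face validity, and measurement error in it would leave residual bias. Nor does a child-level covariate remove differences between hospitals.

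A reader might also infer a multiplicity problem, since the scoring method is to "calculate a scale score for the domains and survey as a whole" and there are two follow-up visits. The documents do not support counting every domain and visit as an equal primary test. One primary outcome is named, and the reason given for the scoring method is interest in overall group means.

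Finally, this is a feasibility study knowingly below the size needed for effectiveness. That lowers the severity, but effectiveness is still its first listed aim.

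**Conclusion.** The point holds as a should-fix. The article names ANOVA by group with a specified adjustment set, and that set omits a covariate that the study collects and that matters in a non-randomised comparison. The possible bias is at most 0.12 to 0.21 SD for a 0.3 SD starting gap, and the possible narrowing of the interval is at most from about 0.52 to 0.41 SD at r = 0.6.

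The correlation and the gap are assumptions. The bias runs in the stated direction for any positive r and any gap that the listed confounders leave unexplained. The documents do not show that such a gap exists or how large it is. Because the baseline scores are collected, nothing is lost if the wording is corrected before analysis.

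**What to change.** Replace the ANOVA sentence with wording to this effect: the 3- and 6-month scores will be analysed by ANCOVA, or by a linear mixed model using all available visits, with group, the baseline score of the same outcome and the listed confounders as covariates. The adjusted group difference will be reported with its 95% confidence interval. Keep the raw group means and standard deviations, which the article wants for pooling across studies.

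Add two sentences. One should acknowledge that baseline adjustment reduces but does not remove confounding between hospitals. The other should commit to recording the date of each baseline assessment relative to the first education support received.

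The cost is a few lines of text and one recorded date per child. No new outcome data are needed. ANCOVA is hardly more complex than the stated method; the mixed model is slightly more so, but keeps children who miss one follow-up visit.
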